### Eligibility criteria

The inclusion criteria are: (i) being a medical student or medical intern at any level of training and (ii) giving informed consent. The exclusion criterion is not wanting to participate in the study.

### Interventions

#### Game jam

The intervention will consist of a game jam aimed at creating a low-tech prototype of an educational game to foster cultural safety in medical education. Groups of five or six students or medical interns will create an educational game prototype from scratch. We will follow a six-step game jam protocol based on Macklin’s *Planning your game jam* guidelines[19] (Figure 1).

**
[figure not shown]
Figure 1. Game jam protocol**

1) Preliminary lecture session (one hour): this is comprised of:

(i) A 30 minute lecture on cultural safety will follow a cultural safety curriculum co-designed with local community members knowledgeable about cultural and traditional health practices[20]; and (ii) a 30 minute lecture on game design.

2) Opening ceremony: game jams usually start with opening comments from the host. We will welcome the participants and share the agenda and rules of the game jam.

3) Game building (four hours)**:** this is comprised of six steps:

a) We will invite participants each to write a brief narrative of when they witnessed (or heard of) discrimination or disrespect against a patient because of their traditional health practices, and the consequences of this discrimination.

b) Participants will share their brief stories within their game jam group to discuss and select the story (based on consensus) that best describes discrimination or disrespect against a patient. A key component of this step is to imagine/brainstorm the fullest range of possible consequences – from trivial to life-threatening.

c) Participants will anonymise the selected story as that of a fictional medical student who has to do a primary care clinical rotation in a local community where she/he faces intercultural tensions in clinical practice. The participants will then convert this narrative into a game, and will define a set of rules, rewards, and penalties.

d) Participants will discuss the factors that hypothetically led the medical student to be discriminatory or disrespectful towards their patient in the story. After the discussion, each group will select and integrate 5-10 factors into the game. The *challenge* here is that players have to become aware gradually that these factors can lead to disrespect or discrimination against culturally diverse patients as they play the game. Concretely, the jammers will be expected to add factors such as the hegemony of evidence-based medicine, colonization and ethnocentrism, and other factors defined in the co-designed cultural safety curriculum.

e) Participants will discuss what can be done to address each of the selected factors that contributed to the disrespect or discrimination experienced by the patient in the narrative. Each group will select and integrate 5-10 actions to promote dialogue and respect towards culturally diverse patients in clinical encounters into their game. The *challenge* is that players learn to respect patients who use traditional health practices in clinical encounters as they play the game.

f) The students will discuss and identify ideas to start working with the patient as a team in the health care decision-making process. This involves engaging in dialogue with the patient to invite them to bring their cultural and traditional practices to inform the health care decision-making process. The traditional practices will be pre-defined by our co-designed curriculum.[20] The *challenge* is that players of the game have to learn how to work with traditional medicine users to jointly make health decisions that are culturally safe.

4) Game testing (one hour)**:** groups will learn from each other’s solutions, ideas, and resources, thus strengthening the cultural safety learning process. At least one member of each group will stay at their workplace to present their game. The remaining students of the group will rotate to play the games created by other groups, thus ensuring that participants from all groups will play at least two additional games. Before the end of the session and using Google Forms, we will ask the students to evaluate other groups’ games in different categories aligned with each of the challenges.

5) Game refining (30 minutes)**:** after playing and testing other teams’ games, each group will have new ideas for refining their own game. Groups will then return to their workplace and apply lessons to improve their own game. Each group will fill a form to register their game on Google Forms.

6) Closing (one-and-a-half hour): we will bring the full group together for final presentation of the games. Each group will have to provide a brief description of their game and to discuss how they solved each of the game building challenges. We will facilitate this session to highlight the underlying concepts of cultural safety. Finally, we will award prizes in three different categories aligned with each of the challenges.

#### Control

The control group will receive a one-and-a-half-hour lecture on cultural safety in medical education by an expert in cultural safety. The lecture will be a standard lesson using PowerPoint slides and will cover the same key concepts used in the game jam, including (a) definition of cultural safety; (b) consequences of cultural tensions in health care; (c) self-awareness; (d) Colombian cultural health practices; and (e) respect for culturally diverse patients. The lecture will be based on our co-designed curriculum.[25] The session will be followed by a 15-minute period to make comments and to ask questions and a 15-minute break.

After the break, the students will participate in a six-hour workshop based on cultural safety selected readings. Groups of five or six students or medical interns will answer ten open-ended questions based on the lecture and the readings, and will create a poster to graphically display their responses to other students. Similar to the game jam session, we will split each group and encourage a rotation process where participants from all groups will learn from at least two additional posters. Before the end of the session and using Google Forms, we will ask the students to evaluate other groups’ posters in different four categories: creativity, coverage of the topic, graphics and pictures, and layout and design.

In the closing session, the best groups will present their posters to the group at large. In this session, we will unpack and highlight the key concepts of cultural safety. Similar to the game jam session, we will award prizes in the four evaluated categories. Matching that in the intervention, the duration of participation in the control group will be 8 hours.

### Criteria for discontinuing or modifying allocated interventions

Participants are free to withdraw from the trial at any point. We will collect reasons for withdrawal from subjects who drop out of the trial.

Participants will not be able to switch groups once they have been randomised to the intervention or control arms, even if they request to do so. Using participants’ lists, the facilitators will ensure that participants remain in their designated groups.

### Strategies to improve adherence to intervention

We will recruit ten to twenty game jam facilitators to support participants and to ensure all groups are able to meet the challenge of each step of the game jam protocol. The facilitators will be final-year medical students or medical interns interested in cultural safety research or game-based learning. We will train the facilitators during one month before the game jam to ensure that they will have the skills successfully to support the game jam participants in their learning process.

We will record the attendance to the intervention and control arms activities. Along with the names of the participants, we will record the date, hour, and their signatures.

### Relevant concomitant care and interventions that are permitted or prohibited during the trial

Contamination is a concern of parallel-group RCTs in education. This occurs when individuals that are receiving the intervention “leak information” that influences results in the control group. This usually reduces the measured intervention contrast, making it more difficult to find a significant difference between groups.[21]

In this study, we cannot guarantee that contamination will not occur, but we will attempt to minimize this risk. We will ask the students to avoid real-time communication with their peers (for example using their cell phones) and will conduct intervention and control activities simultaneously, with the two groups in auditoriums in different buildings. Both groups will have different lunch times.

### Outcomes

Primary outcome: our primary outcome will be students’ self-reported intended patient-oriented behavior. Our outcome is self-reported because it uses students’ opinion regarding their perceived change; intended, because we are assessing students’ planned behavior instead of actual practice/action; and patient-oriented because we measure responses to clinical scenarios indicating intended behavior change. We will assess intended behavior change from the baseline to immediately following the teaching session, from immediately following the teaching session to six months post-intervention, and from the baseline to six months post-intervention.

We will use the CASCADA model of planned behavior to inform our primary outcomes.[22] The model includes the following variables: **C**onscious knowledge was the response to the statement: Considering the cultural beliefs of my patients is not important for health-decision making. **A**ttitude to cultural safety was derived from the statement: It is not worth considering the cultural beliefs of my patients to improve their health. **S**ubjective norm used the statement: Although many physicians disapprove cultural beliefs, I think that these beliefs could improve my patients’ health. Intention to **C**hange derived from the statement: I do not think that learning about cultural beliefs is necessary to provide good health care to my patients. **A**gency was the response to the statement: I feel prepared with the knowledge and skills to prudently incorporate my patients' cultural practices in the health-decision making process. **D**iscussion derived from the response to the statement: I will discuss cultural safety with other students and physicians so they can prudently incorporate their patients' cultural practices in the health-decision making process. Agency and Discussion replace perceived behavior in a conventional theory of planned behavior.[23] Agency involves both self-efficacy and collective efficacy. The CASCADA model includes Discussion as an additional factor that facilitates behavior change.[24] **A**ction was the response to the statement: I will never be open to include my patients’ cultural beliefs and practices in the health-decision making process. Participatory research experts have successfully used the CASCADA model to explore dengue prevention behavior in previous trials.[24]

Secondary outcomes: (i) students’ confidence (transcultural self-efficacy) in their general transcultural skills; and (ii) qualitative understanding of the impact of the intervention in the clinical practice of medical students and medical interns through the Most Significant Change Technique. We will assess transcultural self-efficacy in the baseline, immediately following the teaching session, and six months post-intervention, and we will conduct the qualitative assessment in both groups six months after the intervention.

Output: each student group of the intervention arm will create a co-designed low-tech prototype of a serious game to foster cultural safety in medical students. Some of these prototypes may serve as blueprints for future fully developed games, or as input for future educational videogames.

In addition to the quantitative outcomes of the RCT, we will use the qualitative Most Significant Change narrative technique[25] to collect and analyze stories of change from the medical students six months after the intervention. This technique will allow us to capture meaningful changes in the students’ clinical practice, which may not be apparent from the quantitative evaluation.

### Participant timeline

Figure 2 shows the CONSORT flow diagram of the RCT.[26]

**Figure 2. CONSORT flow diagram of the RCT**

**
[figure not shown]
**

### Recruitment

We will contact the medical students and medical interns using *La Sabana* University’s mailing lists and will e-mail invitations for voluntary participation in the project. For those willing to participate, we will send further information about the project as well as the date and place of the intervention. We will ask interested students to complete the online informed consent and baseline questionnaire one week before the RCT.

### Allocation

A potential source of bias in our study is a possible imbalance in the level of cultural safety training between the intervention and control groups before the intervention. The reason for this issue is that in Colombia around 40% of the population uses cultural and traditional practices to maintain their health.[28] Therefore, some students will be familiar with traditional health practices, probably making them more likely to embrace the cultural safety approach compared with students not familiar with these practices.

To address this potential bias, we will use stratified randomization by cultural safety score at baseline. Based on the preliminary results of the baseline survey, we will split the group of medical students into two groups: low and high level of cultural safety knowledge. Computerized randomization will allocate the students either to the intervention or control arm and we will use equal allocation between treatment arms. The study coordinator will be responsible for generating the allocation sequence, enrol participants, and assign participants to interventions.

### Data collection methods

Data collection: we will collect quantitative data at three time-points: baseline, immediately after the intervention, and six months after the intervention, and will collect the narratives of change only after six months of the game jam. Participants will enter quantitative data using mobile devices and SurveyMonkey self-administered questionnaires. Similarly, they will upload their stories of change using a pre-designed format on Google forms. We report our online instruments in accordance with the Checklist for Reporting Results of Internet E-Surveys -CHERRIES-[29] (Multimedia Appendix 2).

Instrument and quantitative data to be collected: to the best of our knowledge, there are no validated research instruments to measure cultural safety outcomes in healthcare providers. A recent systematic review[30] exploring instruments to assess cultural competence (and aligned concepts) identified ten instruments. All of them were self-administered and based on respondent perceptions. Most of these instruments (5/10) measured cultural competence; none were designed to measure cultural safety.

Our recently published scoping review identified that the Transcultural Self–Efficacy Tool — Multidisciplinary Healthcare Provider version (TSET–MHP) has been used to assess the effectiveness of game-based learning interventions to promote cultural competence.[31] Researchers report a growing body of evidence supporting validity and reliability of the instrument.[32] The instrument assesses cognitive, practical, and affective learning dimensions that can be categorized within the classic knowledge, attitudes, and skills behavior change outcomes.

Brascoupé points out that cultural competence provides a foundation for cultural safety.[33] Ramsden sees cultural safety training as a dynamic process moving from cultural awareness to cultural competence to cultural safety.[3] Following this rationale, we will use a 30-item instrument comprised of three parts. The first part (five items) will explore sociodemographic factors of the students. This includes sex, age, level of training, place of birth, socioeconomic status, and traditional health practices used in the family. The second part (15 items) will be based on the Likert-type TSET-MHP and will explore knowledge, attitudes, skills, and behaviors of cultural competence.

For the third part of the instrument (cultural safety), we developed a Likert-type preliminary version based on our CASCADA variables (see primary outcome) and piloted it for validity and reliability in our pilot RCT.

Validity and reliability: using data from our pilot RCT, we followed the process proposed by Jeffreys[34] to improve the validity and reliability of the third part of our instrument. In the pilot study, the questionnaire included the open question: *how can we improve this instrument?* An inductive thematic analysis[35] of responses identified suggestions to adjust our survey. We shared the adjusted version of the instrument by email with two general practitioners, one medical intern, six medical students, and four cultural safety experts. We adjusted the instrument according to their comments and agreed on the content validity of the instrument by consensus.

To increase the construct validity of our instrument, we used the contrasted group approach, which explores the difference between two separate groups.[34] To increase the predictive validity of our instrument, we looked at the score difference between two timeponts.[36] Reliability explores the degree of accuracy and consistency in measurement. Using R Studio v1.1.419, we calculated Cronbach’s alpha[37] to determine the internal consistency of our instrument. Since our instrument was short (<10 items), we expected a value of >0.5.[38] We complemented the reliability exploration using the test-retest method to explore the stability of the instrument.[34] We report the validity and reliability results of our instrument in the pilot RCT, which is not yet published.

Qualitative data to be collected: to explore students’ stories of change after cultural safety training, we will use the Most Significant Change approach, which is a narrative technique that allows participants to communicate changes most meaningful to them.[39] Using a pre-defined format in Google forms, we will ask participants to write down and enter their stories based on the following questions: *(a) what do you believe was the most significant change in your clinical practice as a result of your participation in the activity [game jam or standard lesson] 6 months ago? (b) can you please share a real-life story depicting this change? (c) why do you think this story is significant?*

The instructions will make clear that participants should feel free to write down stories of negative changes or to say that they did not experience any change at all. Only medical students involved in clinical practice and medical interns (third to seventh year of medical school) will be invited to participate in this part of the RCT.

Methods to maximise completeness and quality of data: The study coordinator and facilitators will be physically present while collecting the data at each time point to ensure the completeness of data. Additionally, we will use several validation options to increase the quality of the data: specific number range, specific character range, date validation, email address format, and prompts that alert participants when they enter incomplete or invalid answers.

In this study, the familiarity of millennial medical students with technology and computer-based education supports using Web-based questionnaires, which reputedly decrease social desirability bias.[40] Assured of anonymity, respondents should be less concerned about what others may think about their responses, including peers and professors.[41] Data reliability in Web-based questionnaires is reportedly equal to or better than traditional paper-based approaches.[42] Examples include data on self-reported perceived health status, oral contraceptive use, and smoking and alcohol use. Web-based questionnaires are also faster to complete and typically cheaper than traditional approaches, making them ideal for our research.

Methods for ensuring secure storage of data: SurveyMonkey and Google responses are stored in a worksheet that can only be accessed through an account login. Data transmission uses Secure Sockets Layer to encrypt information during transport. The data storage is as secure as most other systems that store survey information. After downloading the data, we will delete it from SurveyMonkey and Google Forms. We will be responsible for ensuring the data are securely stored for seven years and then destroyed in accordance with CIET guidelines for security, storage, and eventual destruction of data records.[43]

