| **Development and pre-testing** | Development and testing | We will use a 30-item instrument comprised of three parts. The first part (five items) will explore sociodemographic factors of the students. The second part (15 items) will be based on the Transcultural Self–Efficacy Tool and will explore knowledge, attitudes, skills, and behaviors of cultural competence. For the third part of the instrument (cultural safety), we developed a Likert-type preliminary version based on our CASCADA variables (see primary outcome) and piloted it for validity and reliability in our pilot RCT.  Regarding the qualitative data, using a pre-defined format in Google forms, we will ask participants to write down and enter their stories. |
| **Recruitment process and description of the sample having access to the questionnaire** | Open survey versus closed survey | Closed survey sent by institutional email from *La Sabana* University. |
|  | Contact mode | Contact with participants online through e-mail and face-to-face. |
|  | Advertising the survey | Not applicable. |
| **Survey administration** | Web/E-mail | E-mail survey using SurveyMonkey and Google Forms. There was an automatic method for capturing responses. |
|  | Context | We will contact the medical students and medical interns using *La Sabana* University’s mailing lists and will e-mail invitations for voluntary participation in the project. |
|  | Mandatory/voluntary | Voluntary survey. |
|  | Incentives | Participants of the qualitative component of the study will enter a raffle after submitting their story. We will offer one gift card of CAD 20 for every ten stories collected. |
|  | Time/date | July 2019 to July 2020. |
|  | Randomization of items or questionnaires | Stratified randomization by cultural safety score at baseline. |
|  | Adaptive questioning | Not applicable. |
|  | Number of items | 30 items in total. |
|  | Number of screens (pages) | Three Webpage per survey. |
|  | Completeness check | We will use several validation options to increase the quality of the data: specific number range, specific character range, date validation, email address format, and prompts that alert participants when they enter incomplete or invalid answers. |
|  | Review step | Respondents were not able to review and change their answers. |

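### Facilitators are in the room while the self-reported primary outcome is answered, and the anonymity relied on to limit social-desirability bias is not something the design can provide

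*Protocol*

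**What the plan says.** In the Protocol, Data collection methods, the paragraph on completeness and quality states: "The study coordinator and facilitators will be physically present while collecting the data at each time point to ensure the completeness of data". The paragraph after it argues that web questionnaires reduce social-desirability bias: "Assured of anonymity, respondents should be less concerned about what others may think about their responses, including peers and professors".

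Who the facilitators are is set out in two places. Strategies to improve adherence to intervention says: "We will recruit ten to twenty game jam facilitators to support participants". These are students in their last year or interns with an interest in the subject or in game-based learning, and they receive a month of training. The Discussion separately places five facilitators at each arm's site, to keep participants in their assigned groups.

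On linkage, Allocation says that "we will use stratified randomization by cultural safety score at baseline", and makes the study coordinator responsible for both the sequence and the assignment. The form checks listed under Data collection methods include "specific number range, specific character range, date validation, email address format".

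On the baseline wave, Recruitment says: "We will ask interested students to complete the online informed consent and baseline questionnaire one week before the RCT". The CHERRIES appendix gives the mode as "E-mail survey using SurveyMonkey and Google Forms" and the contact as "Contact with participants online through e-mail and face-to-face".

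Methods for analyzing data puts both between-group and within-group t-tests in the primary analysis.

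**The concern.** The respondent is the assessor of the primary outcome. The statements listed under Outcomes are transparent: a student who has just spent eight hours on cultural safety can see which answer is approved of. The only safeguard the protocol offers is that respondents feel unobserved by peers and teachers. The collection procedure brings peers and seniors into the room, and some of them may have coached the respondent's own group that day.

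If this presence moves answers equally in both arms, the randomised comparison is unaffected, but within-arm changes from baseline could be distorted if baseline was answered under other conditions. If it moves answers unequally, the between-arm estimate is biased, and neither a larger sample nor a multiplicity adjustment removes that.

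**Working it through.** **1. Presence against anonymity.** The two statements stand in consecutive paragraphs of Data collection methods. The first puts the coordinator and facilitators at every wave. The second relies on respondents not worrying about peers. Under Strategies to improve adherence, the facilitators are peers or seniors of the respondents. The safeguard and the procedure therefore pull in opposite directions.

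**2. Are the answers anonymous?** No. Stratifying by baseline score means that each score was tied to a named student before assignment. That is decisive by itself. The e-mail format check is only weak support, because the protocol does not say that an address is entered alongside the outcome items. The data are at best confidential and coded, and no coding scheme is described.

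**3. Are conditions the same in both arms?** The protocol does not say. Ten to twenty facilitators support the game jam, and five stand at each site. It is not stated whether these groups overlap, which of them attend data collection in which arm, or who attends at six months. The arms run at the same time in different buildings, so one coordinator cannot be in both unless the questionnaires are staggered.

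**4. Was baseline supervised?** Recruitment and the CHERRIES survey mode suggest an e-mailed online form a week earlier. The presence statement covers every time point. All quantitative waves are completed online on mobile devices, the Ethics section has facilitators checking online consent, and CHERRIES lists face-to-face contact. A supervised online baseline is therefore possible. This is a tension to reconcile, not a proven contradiction.

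**5. Scale.** Inputs from Sample size: means 26.9 and 25.9, SD 4. Difference = 26.9 − 25.9 = 1.0 point; d = 1.0/4 = 0.25, as the protocol states. The planned arm size of 199 is taken as given. (A two-sided calculation at d = 0.25 and 80% power gives 252 per arm, and a one-sided one gives 198. That is a separate matter.) Results reports 640 randomised, which at 1:1 is 640/2 = 320 per arm.

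Standard error of the between-arm difference = 4 × √(2/n):
- n = 199: 0.401; smallest significant difference 1.96 × 0.401 = 0.79 points
- n = 320: 0.316; smallest significant difference 1.96 × 0.316 = 0.62 points

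Suppose there is no true effect and the arms differ in reporting bias by b points. The documents give no value for b, so the range is an assumption. The probability of a significant result is Φ(b/SE − 1.96) + Φ(−b/SE − 1.96):

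| b (points) | share of 1.0 | 199 per arm | 320 per arm |
|---|---|---|---|
| 0 | 0% | 5% | 5% |
| 0.25 | 25% | 9.6% | 12% |
| 0.5 | 50% | 24% | 35% |
| 0.75 | 75% | 46% | 66% |
| 1.0 | 100% | 70% | 89% |

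These use an unadjusted two-sided 5% test. Holm adjustment would lower them.

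**6. A shift c common to both arms.** Between arms, (game jam + c) − (control + c) leaves the difference unchanged, so that test stays at 5%. Within an arm, the SD of change is 4 × √(2(1 − ρ)) and its standard error is that divided by √199. With c = 0.5 and no true change, both c and ρ being assumptions:
- ρ = 0.3: SD 4.73, SE 0.336, false positives 32%
- ρ = 0.7: SD 3.10, SE 0.220, false positives 62%

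This applies only if the baseline setting really differed from follow-up.

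**The case against.** Several points can be made for the protocol, and some of them stand.

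- **Direction.** A reader might infer that the bias is stronger in the game jam arm and so favours the hypothesis, because that arm has the trained helpers. The documents do not support this as a conclusion. The collection procedure is described once, without distinction by arm. Five facilitators stand at each site, and nothing says who collects data where. Control participants also meet an expert lecturer, a closing session and prizes, so there is pressure to please in both arms. The direction is plausible, not shown.
- **Baseline.** A reader might also infer that baseline was unsupervised. Online does not mean unsupervised in this protocol, as step 4 shows. A change of setting common to both arms would in any case leave the randomised comparison intact.
- **Presence is not observation.** Questionnaires are self-administered on mobile devices. Five facilitators per site means one for about 40 of the planned 200 participants per arm (200/5), or 64 at 320 per arm (320/5). Nothing says that facilitators see the answers. This weakens the concern but does not restore anonymity.
- **Size.** The bias figures are assumptions with no anchor in the documents. This is correct, and they show scale only.
- **Completeness.** On-screen prompts help only someone who has opened the form. Presence may also prevent non-submission, so removing it has a cost.

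What none of this answers is that the protocol rests its defence on an anonymity that its own randomisation rules out, with peers or seniors in the room.

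**Conclusion.** The point holds as a risk of social-desirability bias in the self-reported primary outcome, possibly differential by arm. It rests on three things the protocol states: facilitators are present when answers are given, those facilitators are senior students or interns of whom some support the game jam groups, and baseline scores are identifiable because they set the stratum.

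The documents establish neither the direction nor the size of any bias. If the arms differed by an assumed 0.25 to 0.5 points, that would be a quarter to a half of the planned 1.0-point difference. The false-positive rate would be 9.6% to 24% at 199 per arm and 12% to 35% at 320, before Holm adjustment. A shift equal in both arms matters only for the within-arm comparisons, and only if the baseline setting differed. This is an improvement worth making because it is cheap; it does not show that the between-arm result is invalid.

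**What to change.** 1. In Data collection methods, for every wave still open, have facilitators who coached or taught participants step away while the questionnaires are answered.
2. Use the same conditions in both arms. Keep on hand only existing personnel who did not coach or teach that group, for example one of the five site facilitators in each building. State who is present by arm and wave, and say how the ten to twenty game jam facilitators relate to the five per site.
3. Keep the on-screen prompts and check at the exit that each form has been submitted, without viewing the answers.
4. Replace the appeal to anonymity with an accurate description: confidential, linked by participant code.
5. Reconcile Recruitment and the CHERRIES survey mode with the claim of presence at every wave by stating how baseline was actually supervised. If its setting differed from follow-up, do not read within-arm changes from baseline as intervention effects.

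Baseline is already complete according to Results, so for waves that have closed only the reporting in items 2, 4 and 5 applies. The cost is an instruction to facilitators and some rewording, with no added staff. The downside is less help on the spot and possibly slightly lower completion.
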